### 2.5 Sample size

Through multiple clinical pilot investigations and expert consultations, a standardized participant information collection form has been developed and refined. Additionally, based on a comprehensive review of prior literature and expert discussions, this study has preliminarily identified the characteristic clinical symptoms and physical signs of PMOP-KOA. To estimate the required sample size, the Kendall method was initially applied, multiplying the number of variables by five, yielding a minimum sample size of 150 participants (15). To further enhance methodological rigor, a supplementary power analysis was conducted. Assuming a medium effect size (Cohen’s d = 0.5), a significance level (α) of 0.05, and a power (1–β) of 0.80, the required sample size for detecting group differences was calculated to be approximately 128 participants using standard formulas. Allowing for a 15% attrition rate due to potential loss to follow-up or incomplete data, the final target sample size was set at 150 participants. This dual approach ensures both practical feasibility and statistical robustness.

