**Kellgren & Lawrence (KL) grading**	
No changes (normal)	0
Joint space appears normal (doubtful osteoarthritis)	I
Possible joint space narrowing (mild osteoarthritis)	II
Definite joint space narrowing with sclerosis (moderate osteoarthritis)	III
Severe joint space narrowing with significant sclerosis and bone deformities (severe osteoarthritis)	IV

Traditional Chinese medicine syndromes represent specific stages in KOA or PMOP progression, influenced by both internal and external factors. TCM-based treatment considers an individual’s constitution, environmental conditions, and seasonal changes, following the principle of “treatment based on syndrome differentiation.” This approach is fundamental in TCM, involving the identification of syndromes through symptom analysis and physical examination methods such as inspection, auscultation, olfaction, and palpation. By classifying patients based on syndrome differentiation, TCM provides a framework for stratifying individuals and selecting appropriate treatments tailored to distinct clinical presentations.

According to the Guidelines for the Diagnosis and Treatment of Osteoarthritis (2018 edition) and the Guidelines for the Diagnosis and Treatment of Primary Osteoporosis (2022 edition) issued by the China Association of Chinese Medicine, the primary TCM syndromes commonly observed in patients with KOA and PMOP include yang deficiency, yin deficiency, and combined yin-yang deficiency. In this study, syndrome classification will be conducted by two independent TCM practitioners with senior titles based on a standardized TCM four-diagnostic information collection form (inspection, listening/smelling, inquiry, palpation). In cases of disagreement, a third senior practitioner will be consulted for arbitration. Inter-rater reliability will be assessed using Cohen’s kappa coefficient to ensure diagnostic consistency. Participants will then be classified accordingly, and peripheral blood samples will be collected for high-throughput sequencing analysis.

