### 2.7 Biological sample collection

Blood samples will be collected from participants categorized by the three TCM syndrome classifications using PAXgene™ Blood RNA Tubes (16), with 2.5 mL of venous blood obtained per individual. Immediately after collection, samples will be stored at 4°C and subsequently transferred to a −80°C freezer on the same day following a stepwise freezing protocol. To minimize potential batch effects, all collected samples will be randomly assigned to RNA extraction and sequencing batches. Furthermore, RNA quality will be assessed using the RNA Integrity Number (RIN), and only samples with RIN ≥ 7 will be included in downstream analyses. All samples will be transported to the BGI Biological Sample Testing Center via dry ice cold chain logistics for subsequent RNA-seq high-throughput sequencing (17).

The same batch of blood samples used for RNA-seq will also be used for RT-qPCR validation. RNA (1 μg) will be used as a template for reverse transcription to synthesize complementary DNA (cDNA) (RK20403; ABclonal, Woburn, MA, United States). Target gene sequences will be obtained from the GenBank database, and primers will be designed using PrimerExpress Software v2.0. GAPDH will be selected as the internal reference gene, and its stability across different experimental conditions will be verified using geNorm and NormFinder algorithms. Experimental results will be analyzed using the relative quantification method, with 2^–ΔΔCt^ as the indicator to represent the relative gene expression levels.

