### 2.11 Data management and statistical analysis

Data entry and logical verification were performed by two independent personnel using an electronic management system (National Copyright Registration Number: 2023SR0693141) to handle missing and abnormal values, ensuring data accuracy. Quality control measures were established in accordance with the requirements of clinical epidemiological cross-sectional studies and the specific characteristics of TCM research (21, 22). For standardization, all knee X-ray imaging and BMD assessments for participants from all community sub-centers were conducted at Beijing Electric Power Hospital. All recorded data must be preserved as original records and must not be altered arbitrarily.

Statistical analysis was performed using R 4.3.1. Continuous variables are presented as mean ± standard deviation ($\bar{\text{x}}$ ± s), while categorical variables are reported as percentages. Fisher’s exact test or Chi-square test was used for between-group comparisons. Variance estimation was performed using Taylor series linearization and replication methods. A two-sided *P*-value < 0.05 was considered statistically significant.

To control for potential confounding variables—such as body mass index (BMI), physical activity, dietary habits, and history of estrogen treatment multivariable regression models (e.g., logistic regression or Cox proportional hazards models for time-to-event data) will be employed. In addition, propensity score matching (PSM) or inverse probability of treatment weighting may be used where appropriate to balance covariates among comparison groups and enhance causal inference validity.

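### The 128 behind the target of 150 is a two-group total; the article defines three syndrome groups, so 80% power at d = 0.5 does not hold for pairwise or overall three-group comparisons

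*Protocol article*

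**What the plan says.** Section 2.5 gives two justifications for the sample size. The first is a rule of thumb: "multiplying the number of variables by five, yielding a minimum sample size of 150 participants". The second is a supplementary power analysis with a Cohen's d of 0.5, "a significance level (α) of 0.05" and "a power (1–β) of 0.80", from which "the required sample size for detecting group differences was calculated to be approximately 128 participants using standard formulas". A 15% allowance for loss to follow-up or incomplete data then leads to a final target of 150. The section closes by claiming that the two approaches together ensure feasibility and statistical robustness. It does not say which groups are compared, how many there are, or on which endpoint.

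The groups appear elsewhere. In section 2.3, after Table 1, "the primary TCM syndromes commonly observed in patients with KOA and PMOP include yang deficiency, yin deficiency, and combined yin-yang deficiency", and participants are classified accordingly before sequencing. Section 2.7 says "Blood samples will be collected from participants categorized by the three TCM syndrome classifications". Section 2.10 makes TCM classification and the differential expression analysis that follows the use of the cross-sectional primary outcomes. Under the second inclusion criterion in section 2.4, every participant has both KOA and osteoporosis.

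**The concern.** Cohen's d measures the gap between two means, and a power calculation based on it needs two groups. The article's structure has three. If 128 is a two-group total, each group was meant to have 64 women. Dividing the same women among three syndromes leaves about 43 to 50 per group.

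What is at stake is how a null result will be read. A reader who sees 80% power at a medium effect may take a non-significant syndrome difference as fair evidence that no medium-sized difference exists. If the real power is nearer 62–70%, that inference is weaker than the article suggests. The second justification does not clearly make up for this, because the same number, 150, serves both as a minimum and as a target that already allows for losses.

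**Working it through.** **Inputs.** d = 0.5, α = 0.05, power 0.80, 15% attrition and target 150 are from section 2.5. The two-sided test is from section 2.11. Three groups are from sections 2.3 and 2.7. The split between syndromes is not stated. I assume equal thirds, which maximises power for the weakest of the three pairs.

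**Reproducing the plan's figures.**
- Normal approximation: n per group = 2(1.960 + 0.842)² / 0.5² = 62.8, so 63 per group and 126 in total.
- Exact t-test: 63.77, so 64 per group and 2 × 64 = 128. This matches.
- A one-sided t-test needs 50.15, so 51 per group and 102 in total. This does not match.
- A three-group F-test at the conventional medium f = 0.25 needs 157.2, so 158 in total. This does not match.
- Attrition: 128 / 0.85 = 150.6, in line with the stated 150.

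The arithmetic is therefore sound for two equal groups.

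**Applying it to three groups.** Analysable women: 150 × 0.85 = 127.5 with the full allowance, or 150 with no loss. Per group: 127.5 / 3 = 42.5, or 150 / 3 = 50.

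Pairwise power at d = 0.5 is approximately Φ(d√(n/2) − 1.96):
- n = 42.5: 0.5 × √21.25 = 2.305, and Φ(0.345) = 0.635. The exact t-test gives 0.625.
- n = 50: 0.5 × √25 = 2.5, and Φ(0.54) = 0.705. The exact t-test gives 0.697.

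The overall three-group test has 2 and N − 3 degrees of freedom and noncentrality N f²:

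| Pattern of means | f | N = 127.5 | N = 150 |
|---|---|---|---|
| Conventional medium | 0.25 | 70% | 78% |
| Two groups equal, third 0.5 SD away | 0.236 | 65% | 73% |
| Extremes 0.5 SD apart, third midway | 0.204 | 52% | 59% |

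**Sensitivity to assumptions the article does not state.**
- Bonferroni for three pairs (α = 0.0167) lowers pairwise power to 45% at N = 127.5 and 53% at N = 150.
- An illustrative 50/30/20 split gives the smallest pair 49% and 55%, unadjusted.

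**One syndrome against the other two combined** (t-test, d = 0.5, two-sided 0.05):

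| Share in the single syndrome | N = 127.5 | N = 150 |
|---|---|---|
| 20% | 61% | 68% |
| One third | 75% | 82% |
| 40% | 78% | 85% |
| 50% | 80% | 86% |

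**Effect detectable with 80% power, equal thirds.**

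| Comparison | N = 127.5 | N = 150 |
|---|---|---|
| Pairwise d, unadjusted | 0.61 | 0.57 |
| Pairwise d, Bonferroni | 0.71 | 0.66 |
| Overall f | 0.28 | 0.26 |

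**The rule of thumb.** 150 / 5 = 30 variables. If the minimum means women analysed, 127.5 / 5 = 25.5 supports 25 variables, and keeping 150 would take 150 / 0.85 = 176.5, so 177 enrolled. If it means women enrolled at baseline, 150 meets it.

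**The case against.** The strongest reply is that section 2.5 never says two groups and never says that the calculation serves the syndrome comparisons. Both are inferred, from the use of d, the exact match to 2 × 64, and the absence of any other defined groups. Section 2.11 mentions regression and covariate balancing among comparison groups, and section 2.10 puts fracture incidence first in follow-up, so the full protocol may name some other contrast. This stands as a limit on certainty. It does not rescue the statement, because the article attaches a power figure to no comparison that it describes. A case-control contrast is ruled out, since every participant has both conditions.

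A reader might infer that 80% is false for every syndrome comparison. The documents do not support that. One syndrome against the rest reaches 82–86% with 150 women when a third to a half of them have that syndrome, and such a contrast would suit the search for subtype markers. It is not specified, however, and it falls short for a small syndrome.

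Three further points stand:
- The article states neither a Bonferroni correction nor a group split, so figures that rest on them are illustrations.
- Classification and sequencing belong to the cross-sectional phase, so loss to follow-up need not shrink that comparison. With all 150 women the overall test at f = 0.25 has 78%, only about 2 points short.
- Section 2.11 names no analysis of variance, so the overall F-test is a benchmark and not the planned test.

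A reader might also infer that the study falls below its own minimum sample size. That follows only if the variables-times-five rule counts women analysed after attrition, which the article does not say.

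**Conclusion.** The concern holds in limited form. The figures 128 and 150 are correctly computed, but for two equal groups, while the article defines three. With equal thirds and 127 to 150 analysable women, power at d = 0.5 is about 62–70% for unadjusted pairwise tests, and about 70–78% for an overall test at f = 0.25. The stated 80% is not delivered for these comparisons, even with no attrition. The conclusion rests on the inference that the syndromes are the groups meant in section 2.5, and its size depends on the assumed split.

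The variables-times-five point is secondary and conditional. As written, the claim that the dual approach ensures statistical robustness is not established.

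**What to change.** Keep the target of 150 and revise the wording of section 2.5:

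1. Name the contrast and the endpoint to which the power statement refers.
2. If it is the three syndromes, replace the claim of 80% power at d = 0.5 with the detectable effect. For example: with 150 enrolled and 127 to 150 analysable in three groups of similar size, 80% power is available for a pairwise difference of d of about 0.61 to 0.57 unadjusted, or for an overall effect of f of about 0.28 to 0.26. If pairwise tests will be adjusted by Bonferroni, give about 0.71 to 0.66. State the assumed split.
3. If one syndrome against the rest is intended, say so and give power for the expected share of that syndrome.
4. State that the variables-times-five rule applies to the 150 women enrolled at baseline, or drop the claim that the dual approach ensures statistical robustness.

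The cost is a few sentences. Recruitment and procedures do not change, but the stated detectable effect becomes less favourable. For scale, keeping 80% at d = 0.5 for every unadjusted pair would need 3 × 64 = 192 analysable women, or 192 / 0.85 = 226 enrolled. That expansion is not needed if the claim is restated.

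### The 80% power quoted for d = 0.5 with about 128 women holds only for two equal groups of 64, while the only comparison grouping the protocol defines is three TCM syndromes of uncontrolled size

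*Protocol article*

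**What the plan says.** Section 2.5 of the protocol article sets the target of 150 in two ways. A rule of five participants per variable gives 150. A supplementary power analysis then uses "Assuming a medium effect size (Cohen’s d = 0.5", "a significance level (α) of 0.05" and "a power (1–β) of 0.80", and concludes that "the required sample size for detecting group differences was calculated to be approximately 128 participants using standard formulas". A 15% attrition allowance brings this back to 150. The section closes by claiming that the two approaches together secure statistical robustness. It does not say which groups are compared, how many there are, how large each is, or on what outcome.

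Section 2.4 requires every participant to be a postmenopausal woman with both knee osteoarthritis and osteoporosis. Section 2.3 says that the primary syndromes "include yang deficiency, yin deficiency, and combined yin-yang deficiency", and that participants are classified accordingly. Section 2.7 says "Blood samples will be collected from participants categorized by the three TCM syndrome classifications". Section 2.10 uses the cross-sectional data for TCM classification and then differential gene expression. Section 2.11 sets the test level: "A two-sided *P*-value < 0.05 was considered statistically significant".

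**The concern.** Cohen's d is a difference between two means, and 128 is the familiar total for two equal groups at d = 0.5. The inclusion criteria leave no disease-free, single-disease or male comparator, and no two-group contrast is described anywhere. The one comparison grouping that is defined has three classes, filled as women present. Two groups of 64 would use up all 128 women and leave none for the third syndrome.

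If the stated power is read as applying to the syndrome comparison, a non-significant difference in BMD or another continuous measure would be judged against 80% when the real figure is clearly lower. That would make a null result look more informative than it is.

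**Working it through.** **Inputs from the documents.** d = 0.5, alpha 0.05, power 0.80, about 128 required, 15% attrition, target 150 (section 2.5); two-sided testing (section 2.11); three syndromes (sections 2.3 and 2.7).

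**Assumptions.** The split across syndromes is not stated, so equal thirds and 50/30/20 are shown. The outcome is one continuous measure on independent women, tested by one contrast without multiplicity adjustment. The 15% allowance covers both loss to follow-up and incomplete data. Loss to follow-up does not remove a woman from a baseline comparison, so the evaluable number lies between 128 and 150.

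**Step 1: reproduce 128.** The normal approximation is n per group = 2(1.960 + 0.842)² / 0.5² = 62.8, so 63 per group and 126 in all. The noncentral t gives 63.77, so 64 per group and 128 in all, with power 0.801. The plan's number is therefore the two-equal-group t-test figure. Attrition: 128 / 0.85 = 150.6, consistent with 150. The arithmetic itself is correct.

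**Step 2: three equal groups.** Power comes from the noncentral t with noncentrality d × √(n₁n₂/(n₁ + n₂)), which is d × √(n/2) for equal groups, and n₁ + n₂ − 2 degrees of freedom.

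- N = 128: n = 128/3 = 42.7, noncentrality 0.5 × √21.33 = 2.31, power 62.7%.
- N = 150: n = 50, noncentrality 0.5 × √25 = 2.50, power 69.7%.

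**Step 3: an unequal split (assumed 50/30/20).**

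| N | Group sizes | Largest v middle | Largest v smallest | Middle v smallest |
|---|---|---|---|---|
| 128 | 64 / 38.4 / 25.6 | 68% | 56% | 49% |
| 150 | 75 / 45 / 30 | 75% | 63% | 55% |

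For the first cell: 0.5 × √(64 × 38.4 / 102.4) = 0.5 × √24 = 2.45, power 67.9%.

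**Step 4: a point that does not depend on the split.** A contrast needs 63.77 per group, or 127.5 women in two equal groups, to reach 80%. With 128 evaluable, moving even one woman to the third syndrome leaves 127 for the pair, which is too few. So no pairwise contrast reaches 80% at 128. All three contrasts at 80% would need 3 × 64 = 192 evaluable women.

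**Step 5: three-group F-test at N = 128, outer means 0.5 SD apart.** With the third mean midway, Cohen's f = 0.5 × √(1/6) = 0.204 and power is 52%. With the third mean equal to one of the others, f = 0.5 × √2/3 = 0.236 and power is 65%. At N = 150 the same patterns give 59% and 73%.

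**Step 6: detectable effect at 80% power, equal thirds.** d = 0.61 at N = 128 and d = 0.57 at N = 150.

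**The case against.** The strongest reply is that section 2.5 never ties its 80% to the syndromes. It speaks only of group differences, and other comparisons are planned: section 2.11 refers to unnamed comparison groups for adjusted and propensity-based models, and section 2.10 makes fracture the key follow-up outcome. This stands in part. The link to the syndromes is a strong inference from the only grouping the protocol defines, not a stated fact. It does not rescue the figure, because no contrast of 64 against 64 is described for any purpose.

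A reader might infer that power is at most 63%. The documents do not support a ceiling, because they state neither a split nor the evaluable number at baseline. At 128, the two larger groups reach 71% under an assumed 40/40/20 split. At 150, they pass 80% under an assumed 45/45/10 split (82%), although the other two contrasts then have about 41%. A contrast of one syndrome against the other two pooled, under equal thirds, would have 75% at 128 and 82% at 150, but the protocol describes no such contrast.

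A further objection is that d = 0.5 at alpha 0.05 describes neither transcriptome-wide testing nor the Fisher and chi-square tests that section 2.11 names for between-group comparison. That is right. The percentages here apply to a single continuous outcome such as BMD and must not be carried over to the expression analysis.

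Finally, the power analysis is called supplementary, and the five-per-variable rule had already produced 150. True, but that rule carries no power statement. The only power claim is this one, and section 2.5 rests its robustness claim partly on it.

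**Conclusion.** The concern holds in a limited form. The figure of 128 is computed correctly, but for a two-equal-group design that the protocol does not describe. Applied to the three syndromes, with one unadjusted contrast on one continuous outcome, pairwise power at d = 0.5 is about 63% to 70% under equal thirds and about 49% to 75% under 50/30/20, depending on the contrast and on whether 128 or 150 women are evaluable. With 128 evaluable, no pairwise contrast reaches the stated 80%, whatever the split.

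Two stronger statements do not follow. The protocol does not expressly claim 80% for the syndrome comparison, and 63% is the value for one split at one sample size, not an upper bound.

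**What to change.** Keep the target of 150 and revise section 2.5:

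1. Name the contrast and the outcome that the power calculation is for.
2. State that 128 is the figure for two equal groups of 64.
3. For the three-syndrome comparison of a single continuous outcome such as BMD, replace the 80% with the power range above, or with the detectable effect at 80% power (d about 0.57 to 0.61 under equal thirds). State the assumed split and add a row for an unequal one.
4. State that the figure does not cover the differential expression analysis.
5. Drop the claim that the calculation secures statistical robustness for the syndrome comparison.

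The cost is a rewording and a less favourable stated power. It needs no extra participants and no change to study procedures.

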### 2.6 Bone density assessment

A HOLOGIC Wi dual-energy X-ray absorptiometry (DEXA) scanner (United States) will be utilized to measure bone density at the lumbar spine and bilateral hips, recording the T-score and Z-score at each site. The instrument’s precision will be maintained at 1%, ensuring that the error in repeated measurements remains below 1%. Daily calibration and maintenance will be conducted by trained professionals to ensure measurement accuracy and optimal device performance.

### 2.7 Biological sample collection

Blood samples will be collected from participants categorized by the three TCM syndrome classifications using PAXgene™ Blood RNA Tubes (16), with 2.5 mL of venous blood obtained per individual. Immediately after collection, samples will be stored at 4°C and subsequently transferred to a −80°C freezer on the same day following a stepwise freezing protocol. To minimize potential batch effects, all collected samples will be randomly assigned to RNA extraction and sequencing batches. Furthermore, RNA quality will be assessed using the RNA Integrity Number (RIN), and only samples with RIN ≥ 7 will be included in downstream analyses. All samples will be transported to the BGI Biological Sample Testing Center via dry ice cold chain logistics for subsequent RNA-seq high-throughput sequencing (17).

The same batch of blood samples used for RNA-seq will also be used for RT-qPCR validation. RNA (1 μg) will be used as a template for reverse transcription to synthesize complementary DNA (cDNA) (RK20403; ABclonal, Woburn, MA, United States). Target gene sequences will be obtained from the GenBank database, and primers will be designed using PrimerExpress Software v2.0. GAPDH will be selected as the internal reference gene, and its stability across different experimental conditions will be verified using geNorm and NormFinder algorithms. Experimental results will be analyzed using the relative quantification method, with 2^–ΔΔCt^ as the indicator to represent the relative gene expression levels.

